#### Level 2 data collection

In addition to the Level 1 data, Level 2 sites will be required to provide more detailed, pseudo-anonymised individual patient-level data including age, sex, ethnicity and geographical variables. This form of data collection will also capture non-identifiable clinical information including admission month and year; source of admission; ICD-10 diagnosis codes; Office of Population, Census and Surveys (OPCS) procedure codes; length of stay - total and by ward type; discharge destination; healthcare resource group (HRG) codes; pseudo-anonymised consultant and GP practice codes; re-admission at 28 days for COPD; re-admission at 28 days for all cause admissions; re-admission at 90 days for COPD; out-patients appointments; ED appointments; in‐hospital mortality; 90-day mortality including number of days after discharge that death occurred by data linkage to death registry information and – at implementation sites – the total number of patients in whom the bundle was used. Level 2 sites will also report on process measures associated with the delivery of components of COPD care by returning information extracted from a randomly selected sample of 140 patient records per site.

#### Level 3 data collection

In addition to the Level 1 and 2 data, a selection of sites will form Level 3 case studies and be examined in detail as regards the process of care bundle implementation, the context in which the care bundles are delivered, the impact of the care bundles on staff, patients and carers, and – where more appropriate – the nature of usual COPD care. Data collection at this level will be carried out through non-participant observation and in-depth interviewing, as well as document analysis. It will be supported by the use of topic guides and observation schedules, and conducted by an experienced qualitative researcher at both implementation and comparator sites. Information to inform Level 3 analysis will be gathered throughout the duration of the study, with extended site visits and post-discharge interviews at 30 and 90 days.

### Data management

Standardised templates will be provided to all participating sites with a request that quantitative data for Level 1 and Level 2 is provided in a format as close as possible to that template. A named member of staff at each site will link the different sources of data required at Level 2 (e.g. electronic files, paper-based notes) and supply the resulting information to the study team in a pseudo-anonymised format. Each set of data drawn from an individual patient’s notes will be recorded and linked by a unique, study-specific identification (ID) number, with identification keys held only by the relevant trust, to allow for source data verification as necessary. The qualitative data collected at Level 3 will be anonymised, with unique pseudonyms or identifiers assigned to each participating site or individual, and any identifiable information removed.

All data - including audio recordings, field notes and interview transcripts - will be stored at the University of Bristol, on a secure network drive that it is password protected, regularly backed-up and only accessible by members of the research team. Researchers will use University of Bristol-owned, password-protected laptops to store study information (e.g. typed field notes), while working at participating sites and only the researcher who collected the original data will be able to access information on their particular laptop. Interviews will be recorded using an encrypted voice recorder provided by the University of Bristol and transcription of these data will be conducted by a suitably qualified and approved transcription service.

The custodian of the study dataset will be the Chief Investigator (CI). The study database will be designed so as to protect patient information, in line with GCP guidelines and the Data Protection Act (DPA) 1998 (http://www.legislation.gov.uk/ukpga/1998/29/contents). All individuals recruited to the study will be identified only by a unique patient ID number on any study documentation. Furthermore, research staff will ensure that all participants’ anonymity is maintained through protective and secure handling / storage of information - both within their own research centre and at the participating sites. All documentation relating to the study will be accessible only to study staff and authorised personnel.

### Statistical justification for sample size

The sample size calculation was based on data from Level 2 sites which will be providing pseudo-anonymised details of all individual patient-level admissions over a 12-month period pre- and post-implementation of COPD care bundles. If we have 8 pairs of matched implementation and comparator sites in Level 2, this will provide a sample of around 10,000 admissions per year. Assuming an intra-cluster correlation co-efficient (ICC) of 0.01 and a cluster size of 625 - giving an effect size of 7.25 - there will be greater than 90 % power at the 5 % significance level to detect a 9 % absolute difference in the COPD re-admission rate at 28 days, assuming 30 % of patients are re-admitted in comparator sites.

A random sample of approximately one in five patients will be selected from Level 2 implementation and comparator sites for data on adherence to the care bundles and on delivery of the components of the care bundles. The total sample will be in the region of 2240 (16 × 140) cases. This will provide greater than 90 % power at 5 % significance to detect a difference in adherence to the care bundles from 30 to 70 %. In this case, the sample size has been increased according to a design effect of 29, corresponding to an ICC of 0.02 and a cluster size of 140.

### Data analysis

#### Quantitative analysis of effectiveness data

Level 1 data will be used to calculate the mean change following the introduction of care bundles for each site for all outcome measures. This mean change will be compared between implementer and comparator sites using ordinary linear regression, with adjustment for the following measures from the first period: number of COPD admissions, 28-day re-admission rate, and COPD mortality rate.

Level 2 data will be used in a series of appropriate regression models - depending on the outcome type - to compare the difference in change between the implementation and comparator groups. These models will include a ‘group x time-period’ interaction term to estimate the difference in change in outcome between the implementation and comparator sites before and after implementation of the care bundles. This approach will reflect the fact that the samples in the ‘before’ and ‘after’ periods will have captured data from sets of predominantly different individuals. All models will take appropriate account of the matched design by including indicator variables to distinguish each pair of sites. This will accommodate any between-site variation i.e. clustering, in outcomes. If it proves possible to identify patients who are admitted several times during the study period, a sensitivity analysis will be conducted with just the first of their admissions included, and the primary analysis elaborated if necessary to accommodate any correlation in outcome between a single patient’s episodes of care.

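### Pair indicators do not deal with clustering in the Level 2 models: each hospital's own drift between the before and after years has no error term, so the group-by-period test is too liberal

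*Protocol article*

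**What the plan says.** All references are to the protocol article.

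- *Quantitative analysis of effectiveness data*, Level 2 paragraph: regression models suited to each outcome type, with a group-by-period interaction "to estimate the difference in change in outcome between the implementation and comparator sites before and after implementation of the care bundles".
- Same paragraph, on clustering: "including indicator variables to distinguish each pair of sites. This will accommodate any between-site variation i.e. clustering, in outcomes". No site term, site-by-period term or site-clustered variance is named. The only other provision for correlation concerns repeat admissions of the same patient.
- *Statistical justification for sample size* sizes the same Level 2 data on the basis "If we have 8 pairs of matched implementation and comparator sites in Level 2", and adds that "this will provide a sample of around 10,000 admissions per year". It allows for site-level clustering: "Assuming an intra-cluster correlation co-efficient (ICC) of 0.01 and a cluster size of 625".
- *Outcomes and outcome measures*, and the Level 1 paragraph of the analysis section: the primary 28-day re-admission outcome is analysed as one mean change per site, compared between arms by linear regression.

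**The concern.** Bundle use varies by hospital and by year, not by patient. The noise against which a difference in change must be judged is therefore how much individual hospitals' rates move between two years for reasons unrelated to bundles. The clustering device named in the plan contains none of that. Eight pair indicators take up 7 of the 15 between-site degrees of freedom and the group term takes 1. The other 7 are unmodelled, and so is all independent site-by-period variation.

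Followed as written, the model treats about 20,000 admissions (10,000 a year for two years) as independent, given pair, group and period. If hospitals drift, the Level 2 intervals are too narrow and the P values too small. This matters because the sample size is justified on Level 2, and a falsely precise Level 2 result could overshadow a correctly wide Level 1 result.

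**Working it through.** **Inputs from the article:** 16 sites (8 per group); m = 625 admissions per site-year, so 5,000 per group per period; ICC = 0.01; 28-day re-admission 30%, so v = 0.3 × 0.7 = 0.21; 5% significance, taken as two-sided.

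**Assumed, because the article does not give it:** r, the correlation between a site's effect in the before year and in the after year. It is shown from 1 (no drift) to 0.

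**1. Reproducing the plan's figure.** The design effect is 1 + 624 × 0.01 = 7.24 (1 + 625 × 0.01 = 7.25). The article prints this as "giving an effect size of 7.25". The effective sample is 5,000/7.25 = 690 per group. Power for a 9-point difference is about 97% for 30% vs 21% and 94% for 30% vs 39%. This agrees with the statement "there will be greater than 90 % power at the 5 % significance level". The sample-size section thus expects material clustering by site.

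**2. Variance of the difference in change.**

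- True variance of one site's change: 2v(1 − ICC)/m + 2(1 − r)·ICC·v.
- True variance of the group-by-period contrast: 2/8 of that.
- Variance that the pair-indicator model reports: 4v/5,000, whose square root is 0.0130.
- Ratio of true to reported: (1 − ICC) + m·ICC·(1 − r) = 0.99 + 6.25(1 − r).

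The true size of the nominal 5% test is 2[1 − Φ(1.96/√ratio)].

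**3. Results.** The simulations used a logistic model with pair indicators, group, period and their interaction, under no effect, for 16 sites over two years. Three separate sets of runs were made (one with 4,000 replicates per setting, and one with 1,500 and varying site sizes). The last column gives the range across the sets that covered each setting.

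| r | Variance ratio | SE ratio | Type I error, formula | Type I error, simulated |
|---|---|---|---|---|
| 1 | 0.99 | 0.99 | 4.9% | 4.8–5.3% |
| 0.95 | 1.30 | 1.14 | 8.6% | 8.4–9.6% |
| 0.9 | 1.615 | 1.27 | 12.3% | 11.5–13.1% |
| 0.8 | 2.24 | 1.50 | 19.0% | 18.9–20.1% |
| 0.5 | 4.115 | 2.03 | 33.4% | 32.0–35.5% |
| 0 | 7.24 | 2.69 | 46.6% | 46.6–46.7% |

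At r = 0 the understatement of variance equals the design effect used for sizing. Site-level t-tests on the same simulated data gave 4–6% throughout.

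**4. Sensitivity to the ICC.** At r = 0.8, simulated type I error is 12.8% with ICC 0.005 and 29.7% with ICC 0.02.

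**5. Which part of the omission does the damage.**

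- With r = 1, sites still differ stably within pairs, yet the test holds its size, because stable differences cancel in the before-after contrast.
- If site sizes are also unequal and volumes shift between years (assumed coefficient of variation 0.3 and log-SD 0.2, with no site variance shared within pairs), the error rises only to 6.8%.
- Replacing the pair indicators with 16 site indicators at r = 0.8 gives 19.0%, against 18.9%, so it is no cure.

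Drift between years accounts for nearly all of the inflation.

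**The case against.** **The primary outcome is analysed elsewhere.** This stands. The Level 1 comparison uses one change per site, so its unit of inference is already the site. A reader might infer that the trial's primary result is invalid; the article does not support that. The Level 2 models still matter, because they carry the stated power.

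**Pair indicators fail to separate the two hospitals, so that must be the fault.** A reader might infer this too. The indicators do fail to separate them, but step 5 shows that stable within-pair differences hardly affect the interaction.

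**The size of the problem is not known.** This stands as a limit. It depends on r, which the article does not give, and on the ICC. If hospital rates are very stable the inflation is mild. The calculation also covers one binary outcome. A reader might extend the same percentages to length of stay, mortality or cost, but the article gives no ICC for those.

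**A condensed article leaves variance estimation to the analysis plan.** This stands in part: no full model specification or variance estimator is given, so independence of admissions is what follows from the text, not something it states. But the article does not leave clustering open. It declares clustering dealt with by the pair indicators, and an analysis plan that follows it would inherit the error.

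**The two sections do not contradict each other in intent.** Agreed. Both mean to allow for clustering; the device named in the analysis section does not do what the sizing assumes.

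**Conclusion.** The point holds for the Level 2 patient-level models. The claim that pair indicators take care of any between-site variation is false, and what matters for the interaction is the missing site-by-period variation. With the plan's ICC and site-year size, the nominal 5% test of 28-day re-admission has a true error of about 8–10% if site effects correlate 0.95 between years, 19–20% at 0.8 and 32–36% at 0.5. It is correct only if hospitals do not drift at all. These figures rest on the assumed correlation, on ICC 0.01, and on the model being fitted with nothing beyond the terms named.

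**What to change.** Delete the sentence claiming that pair indicators accommodate between-site variation. Keep the pair indicators as design covariates only, and name the site as the unit of inference for Level 2, by one of:

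- each site's before-after change, analysed as 8 within-pair differences (7 df) or as 16 site changes in two groups (14 df);
- the patient-level model with random site and random site-by-period effects and a small-sample degrees-of-freedom correction;
- the patient-level model with site-clustered standard errors, corrected for having only 16 sites.

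The first is simplest and matches the Level 1 approach. Adding fixed site indicators alone is not enough.

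No new data are needed, only analysis wording and a little code. The cost is wider intervals: at r = 0.8 the standard error of the difference in change rises from 1.3 to 1.9 percentage points. Power for a 9-point difference in change, Φ(0.09/SE − 1.96) with v = 0.21 throughout, is then 99.6% at r = 0.8 (SE 0.0194), 93% at r = 0.5 (SE 0.0263) and 73% at r = 0 (SE 0.0349). A t reference on 14 or 7 df lowers these somewhat.

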#### Quantitative analysis of cost-effectiveness data

The economic impact of care bundles at Level 1 sites will be evaluated by using trust-level data to describe the cost of COPD care per admission for both the implementation and comparator sites during the ‘before’ and ‘after’ time-periods. Since this analysis will use aggregated trust-level data, a simple unit-costing methodology will be deployed, based on a weighted average of non-elective COPD-related HRG codes. This will be used to estimate the incremental impact of bundles on COPD-related NHS secondary care costs.

A more detailed economic evaluation for the 90 days following the index admission will be undertaken in Level 2 sites. This will involve the estimation of per-patient secondary care NHS costs using a more in-depth HRG unit-costing methodology (www.ncbi.nlm.nih.gov/pubmed/21905152/) where patient-specific resource use will be valued using comprehensive, nationally representative sources e.g. NHS reference costs (https://www.gov.uk/government/publications/nhs-reference-costs-2014-to-2015/), the British National Formulary [21] (BNF) and Unit Costs of Health and Social Care (http://www.pssru.ac.uk/project-pages/unit-costs/2014/). Information on procedures and investigations undertaken during an in-patient stay e.g. x-rays, onward referrals, and drugs prescribed will be collected from a review of medical records and from routine data. The per-patient cost estimate will include the cost of admissions and re-admissions during the 90-day period. Linked information on 90-day mortality (including the number of days between discharge and death) will also be collected. The duration of the interactions between a sub-sample of admitted patients and clinical staff will be recorded in a ‘time and motion’ study at Level 3 sites in order to provide an estimate of the staff time involved in treating COPD patients, which will be costed using the sources described above and used to inform the Level 2 cost-effectiveness analysis.

This information on costs and mortality will allow an estimate of cost-effectiveness to be calculated as a ratio of the difference in NHS secondary care costs between intervention and comparator sites to the between-site differences in 90-day mortality. Uncertainty surrounding this estimate will be quantified using cost-effectiveness acceptability curves (CEACs). We will also use deterministic sensitivity analysis where appropriate.

Information on post-discharge resource use will also be collected from a sub-sample of consented Level 3 patients during telephone interviews. This information will be used to provide a descriptive analysis of differences between types of site in the use of primary care services, community care, and informal care up to 90 days post-discharge.

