### Evidence-based COPD care

Emergency admissions to hospital for long-term conditions - including COPD - form part of the NHS Outcomes Framework [11] and are the subject of a number of admission reduction initiatives [12-14]. It has been suggested that 10–34 % of COPD admissions could be avoided through the implementation of evidence-based care [7, 11]. A Royal College of Physicians Audit conducted in 2003 [15] found that, on average, patients spend 8.7 days in hospital during an admission for COPD but also that there was wide variation in terms of both treatment provision and outcomes amongst hospitals. This disparity was particularly marked in relation to mortality. The audit showed that a significant proportion of the observed variability could be explained by availability and access to expert care and evidence-based interventions which have, in turn, resulted in a reduced length of stay and lower mortality [7]. This, therefore, presents a potential opportunity to improve outcomes for patients with COPD [3] by ensuring that their care is consistently provided to a high standard.

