## Methods

### Study design

The research will use a controlled before-and-after design with nested case studies to compare the outcomes of care following the introduction of care bundles with usual care for patients admitted to hospital with AECOPD. Study sites will participate in up to three different levels of data collection and these are described in the schematic presented in Fig. 1.

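### The Level 2 cost-effectiveness ratio is defined as a between-site difference with no before-period term, unlike the difference-in-change contrast used for Level 2 effectiveness

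*Protocol article*

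**What the plan says.** All references are to the protocol article.

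- **Design** (*Study design*): "The research will use a controlled before-and-after design with nested case studies".
- **Level 2 effectiveness** (*Quantitative analysis of effectiveness data*): the models contain a group-by-period "interaction term to estimate the difference in change in outcome between the implementation and comparator sites before and after implementation of the care bundles", and all of them carry indicators for the matched pairs.
- **Level 1 costs** (*Quantitative analysis of cost-effectiveness data*): trust-level data will "describe the cost of COPD care per admission for both the implementation and comparator sites during the" before and after periods, to estimate the incremental impact of bundles.
- **Level 2 costs** (same section): "A more detailed economic evaluation for the 90 days following the index admission will be undertaken in Level 2 sites". The period from which index admissions are taken is not given. The estimate is then defined as "a ratio of the difference in NHS secondary care costs between intervention and comparator sites to the between-site differences in 90-day mortality", with acceptability curves to express its uncertainty.
- **Matching** (*Allocation to study level and matching of sites*): eight pairs, matched as nearly as can be achieved on number of COPD admissions, 28-day re-admission rate and COPD mortality rate. Cost is not a criterion, and the mortality rate is not stated to be the 90-day rate.
- **Data available** (*Statistical justification for sample size*): Level 2 sites provide "details of all individual patient-level admissions over a 12-month period pre- and post-implementation of COPD care bundles".

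**The concern.** Both terms of the ratio, as worded, contrast groups of hospitals and not changes within them. In a randomised comparison that would be unremarkable. Here hospitals volunteer and are classed by whether they use bundles, and Level 2 implementers must deliver both bundles and be willing to report detailed data. Such hospitals may already differ in cost and mortality for reasons unrelated to the bundle. In *Evidence-based COPD care* the article itself reports wide variation between hospitals in treatment and outcome, and adds: "This disparity was particularly marked in relation to mortality".

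A before-and-after design with controls exists to take out such stable differences. A ratio that omits the before period gives up that protection in both numerator and denominator. The acceptability curve does not restore it, because the curve describes uncertainty around whichever contrast was chosen. The same 16 hospitals could then yield one answer on mortality from the interaction model and another inside the ratio.

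**Working it through.** **What the plan allows to be checked.** No figure is stated for the ratio, and the article gives neither costs nor 90-day mortality. No ratio can be recomputed. What can be shown is how much stable between-hospital difference a between-site contrast could carry under the plan's own cluster assumptions.

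**Inputs**
- Sites: 8 per group (*Statistical justification for sample size*).
- Cluster size: 625 per year, so 8 × 625 = 5,000 admissions per group per period (same section).
- ICC: 0.01, stated for 28-day re-admission and borrowed here for mortality (same section).
- 90-day mortality q: not given; assumed 10%, 15% and 20%.

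**The plan's own figure.** The stated inflation factor of 7.25 (labelled an effect size) is 1 + 625 × 0.01; the usual formula gives 1 + 624 × 0.01 = 7.24. Effective n per group is 5,000 / 7.24 = 691. Power at two-sided 5% is 97.0% for 30% v 21% and 94.1% for 30% v 39%. The claim of more than 90% is reproduced, so the cluster inputs are used as they stand.

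**Structure of the two contrasts.** Let B be the baseline gap between groups and D the bundle effect.
- Between-site difference in the after period: B + D.
- Difference in change: (B + D) − B = D, if B is the same in both periods.

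This holds separately for cost and for mortality.

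**Size of B for mortality, with no bundle effect and ignoring matching**
- Stable component: S = √(ICC × q(1−q)) × √(2/8)
- Sampling SE, one period: E = √(2q(1−q)/5,000)
- Sampling SE, difference in change: E × √2

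| q | S (points) | E (points) | E√2 (points) |
|---|---|---|---|
| 10% | 3.00 × 0.5 = 1.5 | 0.60 | 0.85 |
| 15% | 3.57 × 0.5 = 1.8 | 0.71 | 1.01 |
| 20% | 4.00 × 0.5 = 2.0 | 0.80 | 1.13 |

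Over ICC 0.005-0.02 and q of 10-20%, S runs from 1.1 to 2.8 points. The total SD of an unmatched between-site difference is √(1.5² + 0.6²) = 1.6 to √(2.0² + 0.8²) = 2.2 points, but only the S part is removable by using the before period.

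**How stable must site effects be?** With correlation r between a site's effects in the two periods, the variance of the difference in change is 2(1−r)S² + 2E², against S² + E² for the between-site difference. At q = 10% these are 4.5(1−r) + 0.72 and 2.25 + 0.36 = 2.61, equal at 1−r = 1.89/4.5 = 0.42. At q = 20% they are 8(1−r) + 1.28 and 4.64, again equal at 1−r = 0.42. Unmatched, the difference in change has the smaller variance once r exceeds about 0.58. Matching on mortality would shrink S and raise that threshold.

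**The case against.** The strongest reply is that the sentence lists the components of the ratio and is silent on the estimator. The *Abstract* places costs within the controlled before-and-after design. Cost-effectiveness is a listed secondary outcome. The effectiveness section says Level 2 data will be analysed with a group-by-period term. The Level 1 costing uses both periods, and the Level 2 evaluation is presented as a more detailed one. Describing increments as differences between groups is ordinary shorthand, and a condensed article may leave the estimator to a fuller document.

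This makes a before-and-after intention plausible. It does not replace the definition given: the interaction models sit under the effectiveness heading, 90-day mortality is not itself in the outcome list, and the economic section supplies its own, different contrast. If a difference in change was meant, the sentence still needs correcting.

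Several stronger readings are tempting and are not supported:
- *The ratio is unadjusted and ignores the before period.* The text does not say so; it is silent.
- *The ratio will contradict the effectiveness analysis, or reverse sign.* It could differ. Showing a reversal needs cost and mortality gaps that the article does not give.
- *Baseline imbalance is as large as any plausible bundle effect on mortality.* The article states no mortality effect to compare with.
- *Costs are wholly uncontrolled.* Cost is not matched, but unit costs come from national sources and pairs are matched on re-admission rate, which limits part of the variation.

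It also stands that the illustration borrows an ICC from another outcome and ignores the mortality matching, and that the reported wide variation comes from a 2003 audit of hospitals in general.

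**Conclusion.** The concern holds in a limited form. The Level 2 ratio, as defined, is a between-site contrast with no before-period term or baseline adjustment, out of line with the Level 2 effectiveness models and with the Level 1 costing. Followed literally in non-randomised, approximately matched hospitals, it would let pre-existing differences in cost and mortality pass as bundle effects.

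The size is illustrative only: a stable mortality difference with SD of about 1.5-2.0 points, resting on assumed 90-day mortality of 10-20%, the re-admission ICC and no gain from matching. Nothing comparable can be computed for cost. This is a secondary outcome, but one the article offers to managers and policy-makers, and the inconsistency can be removed before analysis.

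**What to change.** In *Quantitative analysis of cost-effectiveness data*, define incremental NHS secondary care cost and incremental 90-day mortality as the group-by-period estimates, with pair indicators, from the Level 2 before and after data. State that the acceptability curves use the same contrast and respect clustering by site or pair, for instance by resampling sites or pairs.

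Handle separately any cost component with no before-period measure, such as staff time from the time-and-motion study; the planned deterministic sensitivity analysis is one place for it. Check also which period the sampled case notes come from, since the article does not say.

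The cost is mainly wording: Level 2 patient-level data, including HRG codes and linked 90-day mortality, are already planned for 12 months before and after. The statistical price is the √2 increase in sampling SE, with full removal of baseline gaps only if site effects are stable between periods.
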